### Interventions

Patients will be randomized to two groups (Fig. 1) and will start using the allocated respiratory support device immediately. For nasal high-flow, “TNI soft flow 50 or 60” is recommended and will be provided by the trial centre before the start of the study. However, other dedicated nasal high-flow devices may also be used. Such devices must be capable of a flow of at least 50 l/min as well as sufficient heating up to the prongs and humidification. So-called hybrid devices are not permitted. NHF will start ideally with a flow of 40 l/min at 37° and FiO_2_ of 0.4, generally with standard or large sized prongs. Later adjustments according to oxygen saturation or patient comfort (temperature and humidity) at a patient level are possible.

**Fig. 1 Fig1:**
[figure not shown]
Study flow chart according to the Consolidated Standards of Reporting Trials

For patients randomized to the NIV arm, NIV is initialized using a regular oral/nasal mask. Pressure support will be initiated with 18/4 mbar for adaptation and then increased to achieve effective respiratory support while trying not to lose tolerance.

With both devices, oxygen should be supplemented to reach an O_2_ saturation range of 88–92%. Patients should use respiratory support as long as possible, both day and night. The study intervention can be initiated at the emergency room or in intermediate or intensive care or a specialized respiratory medicine ward as mentioned above. The use of either device does not require alteration to usual care pathways (including use of any medication), and these will continue for both trial arms.

Statistical monitoring based on data in the database will take place at regular intervals and include the verification that reasons for switching devices are documented in a timely manner and follow the protocol specification. It will also be used to ensure that investigators provide the duration of device use as a measure of patient compliance. Departures at the site level from protocol specifications will lead to corrective measures.

Patients are covered by insurance while in the trial and after the trial; treatment is at the physician’s discretion but may include the continued use of the prescribed device.

### Study endpoints

The primary endpoint is the proportion of patients with treatment failure within 72 h. Treatment failure is defined by (a) switch to another method of non-invasive ventilation or (b) intubation or (c) death.

It is highly recommended that intubation only be initiated if pH < 7.15 and at least one of the following criteria is met: (i) Glasgow Coma Scale (GCS) < 10, (ii) O_2_ saturation < 85% or PaCO_2_ < 45 mmHg despite FiO_2_ > 0.5 and (iii) respiratory rate > 40 cycles/min.

Switching to another method of non-invasive ventilation should only be considered in the following situation:
One of the following criteria is met within 1 h: decrease in pH by at least 0.06, increase in pCO_2_ by at least 10 mmHg, unacceptable decrease in GCS, increase in respiratory rate by at least 20%, insufficient complianceOne of the following criteria is met after 2 h: unacceptable decrease in pH or pCO_2_, clinically unstable compared to last status (beginning at 4 h), insufficient compliance

The most important secondary endpoints are as follows: (a) proportion of patients that fulfil single components of the primary endpoint (i.e. intubation, switch of device or death within 72 h), (b) proportion of patients intubated within 7 days after hospitalization/randomization, (c) overall survival at 28 and 90 days, (d) (invasive) ventilator-free days up to day 28, (e) (invasive) ventilator-free hours until 72 h or until reaching the primary endpoint (whichever comes first), (f) ICU and hospital lengths of stay, (g) proportion of patients requiring sedation and (h) quality of life at day 28 according to St George’s Respiratory Questionnaire (SGRQ) and the Severe Respiratory Insufficiency (SRI) questionnaire, both of which are validated and standard instruments used in patients with obstructive airway diseases [27–29]. Safety issues of interest are device related intolerance/complications and severe diseases acquired under treatment. Compliance and acceptance of devices will also be investigated.

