### Study population

Patients are eligible for the study if they suffer from AECOPD in the absence of other causes of respiratory failure. Investigators from the pulmonology or emergency wards or from the intensive care unit will briefly describe the trial and obtain informed consent. A concise consent for is available if treatment has to begin imminently, and the full consent is then required at a later point in time. On the consent form, participants are informed in detail about data handling and storage. This trial does not involve collecting biological specimens for storage.

Specific eligibility criteria are as follows.

*Inclusion criteria*
Acute hypercapnic exacerbation of chronic obstructive pulmonary disease with respiratory acidosis (pH < 7.35)pCO_2_ > 45 mmHgage ≥ 18 yearsWritten informed consent

*Exclusion criteria*
Immediate need for intubationpH < 7.15BMI ≥ 35 kg/m^2^Established home-NIV or home-CPAPEnd-stage disease with DNI/DNR orderDiseases that could influence the primary endpoint: e.g. acute heart infarction, cardiogenic lung oedema, acute and massive lung embolism (hypertensive), chronic dialysis with metabolic acidosis, unstable rib fracture influencing ventilation, injury to the face prohibiting use of a face maskAcute disease that precludes participation in the trialTracheotomized patientsPsychological/mental or other inabilities to supply required informed consentParticipation in other interventional trialsSuspected lack of compliance

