### Randomization, recruitment and data collection

Randomization will be performed centrally, via a secure web-based tool. The allocation to the intervention arm (randomization ratio 1:1) uses a minimization procedure with a stochastic component that takes into account trial centre, pH ≤/> 7.3 and BMI ≤/> 30 kg/m^2^. The randomization result forwarded automatically via email to the investigator and the Clinical Trial Centre Leipzig.

Adequate recruitment will be encouraged through regular Newsletters including current recruitment status, regular consultations with trial sites by the monitor/coordinating investigator and trial meetings.

The schedule of study visits and list of parameters collected can be found in Table 1. Within the first 24 h, data are collected at 1, 2, 4, 6, 12 and 24 h after which collection takes place at 36, 48 and 72 h. There is a discharge visit and one at day 7 as well as telephone visits on days 28 and 90.

**Table 1 Tab1:** Schedule for study interventions according to Recommendations for Interventional Trials (SPIRIT) indications

Examination/assessment		Treatment											Follow-up		
	Screening	Visit 0	Visit 1						Visit 2		Visit 3		Visit 4	Visit 5^**a**^	Visit 6^**a**^
Timepoint		0 h	1 h ± 30 min	2 h ± 30 min	4 h ± 30 min	6 h ± 30 min	12 h ± 60 min	24 h ± 60 min	36 h ± 90 min	48 h ± 120 min	72 h ± 180 min	discharge	day 7^**b**^ ± 1 day	day 28	day 90
Informed consent	X^c^											X^d^			
Inclusion criteria/exclusion criteria	X														
Randomization		X													
Patient characteristics (anamnesis, comorbidity)	X														
Medication	X							X^e^		X^e^	X^e^	X			
Clinical parameters (heart rate, respiratory rate, blood pressure, Borg’s scale)	X		X	X	X	X	X	X	X	X	X	X	X		
Adverse events/side-effects			X	X	X	X	X	X	X	X	X	X	X	X	X
Glasgow coma scale (GCS)	X		X	X	X	X	X	X	X	X	X	X			
Blood gas analysis (BGA): pO_2_, pCO_2_, pH, SpO_2_, FIO_2_	X		X	X	X	X	X	X	X	X	X	X	X		
Therapy according to allocated device: device parameters		X	X^6^	X	X	X	X	X	X	X	X	X	X^g^	X^f^	X^f^
Therapy: oxygen supplement		X	X	X	X	X	X	X	X	X	X	X	X^f^	X^f^	X^f^
infection parameters and biomarkers (optional)	X							X^e^			X^e^				

^a^Visits 5 and 6 are conducted by telephone

^b^Assessment of intubation; not applicable, if patient is already discharged since no intubation can be stated in this care

^c^Standard (long) version of informed consent OR concise (short) version of informed consent

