^d^Standard (long) version of informed consent, if patient is still able to give informed consent

^e^All medications within the last 24 h resp. laboratory parameters any time within the last 24 h

^f^A change of device is possible, if switch criteria are fulfilled OR need for intubation criteria are met before 72 h → primary endpoint reached

^g^Ongoing treatment, if patient still hospitalized

The case report form (CRF) will be designed by the ZKS Leipzig in cooperation with the co-ordinating investigator and provided in electronic form (eCRF). In order to facilitate the documentation as per protocol in case of malfunction of the electronic system or any of its components, a paper version of the CRF (interim CRF) will be provided in the ISF (investigator site file). The data on this paper version will be transferred to the eCRF as soon as the electronic system is available again.

The eCRF must be completed shortly after each trial visit according to ISO 14155:2020 chapter 7.8.1 and to enable central monitoring of the trial data.

Access to the data base will be limited to authorised staff and patients will be identified by patient-ID only. Authorization is granted by the site’s investigator using the trial specific staff signature and delegation log. Based on the staff signature and delegation, log access to the eCRF will be granted by the responsible staff at the ZKS Leipzig. Authorised staff members on site will be able to enter and update data as well as finalise data by electronic signature during the conduct of the trial according to a trial specific concept for documentation. All entries and data changes will be tracked automatically including date, time and person who entered/changed information (audit trail). Major correction(s) or major missing data have to be explained.

Each trial centre is initiated by the clinical monitor before start of the study, which means that the implementation of the study is explained and all necessary documents are provided. During trial conduct, central and statistical monitoring procedures will be combined with on-site monitoring visits in order to achieve high protocol compliance and data quality, as well as to ensure patients’ safety and rights. All clinical data are entered by the investigators (or their designated staff) into electronic data collection forms, which are all available in the database. Access to the data base will be limited to authorised staff only after training on the database.

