## Discussion

Guidelines recommend the use of NIV as standard therapy in acidotic hypercapnic AECOPD. NIV has been shown to prevent intubation and reduce mortality [6]. However, in broad clinical practice its use is neither widespread nor routine [4]. The reasons range from lack of expertise, unavailable devices or shortage of staff. Up to 30% of AECOPD patients do not tolerate NIV in acute setting.

NHF has been shown to be effective in different settings and is strongly recommended in acute hypoxemic respiratory failure [32, 33]. Following extubation and in the subsequent time period NHF has been recommended [6]. There is growing interest in the use of NHF in ventilatory failure, but most RCTs in this setting have excluded hypercapnic patients [16–18]. It is therefore not surprising that in these studies the investigators found only small decreases in pCO_2_. Today, there is growing evidence that NHF results in pCO_2_ reduction in hypercapnic patients over shorter time periods [11, 12, 20]. In a small pilot trial in patients with stable hypercapnic COPD over 6 weeks, NHF was found to be not inferior compared to NIV in reducing pCO_2_ [34]. The first randomized controlled trial in chronic hypercapnic respiratory insufficient COPD patients strongly suggested non-inferiority of NHF compared to NIV in terms of decarboxylation and some scales measuring quality of life also showed improvement with NHF [14].

In acute hypercapnic respiratory failure, first data exist, but either study populations were small, inhomogeneous, and most were retrospective without randomized control groups. Comparison to other ventilatory support devices in those areas where NIV is meanwhile well established and recommended by guidelines is lacking. The first randomized controlled trial regarding this aspect was the study by Cortegiani et al. [35] comparing NIV and NHF in 80 hypercapnic patients. The result of this study was non-inferiority of NHF in terms of pCO_2_ reduction, though a non-inferiority margin of 10 mmHg may be considered large.

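### Two CO2 criteria in Study endpoints are misprinted: the after-2 h switch rule lists a fall in pCO2, and an intubation criterion lists a low PaCO2

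*Protocol article*

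**What the plan says.** All references are to the protocol article.

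- **Endpoint (Study endpoints).** Treatment failure is a switch to another non-invasive method, intubation or death within 72 h.
- **Switch within 1 h (Study endpoints).** Among the listed reasons is "increase in pCO_2_ by at least 10 mmHg", alongside a pH fall of at least 0.06.
- **Switch after 2 h (Study endpoints).** The corresponding item is "unacceptable decrease in pH or pCO_2". The other reasons are clinical instability (from 4 h) and insufficient compliance.
- **Intubation (Study endpoints).** It is strongly advised only when pH is below 7.15 and at least one of three further criteria holds. Criterion (ii) is oxygen saturation below 85% or "PaCO_2_ < 45 mmHg despite FiO_2_ > 0.5".
- **How the criteria are used.** Table 1, footnote f, says: "A change of device is possible, if switch criteria are fulfilled OR need for intubation criteria are met before 72 h". Under Interventions, statistical monitoring is to verify that "reasons for switching devices are documented in a timely manner and follow the protocol specification", and site-level departures lead to corrective measures.

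**The concern.** The two switch rules disagree on which direction of pCO2 change is bad. Read literally, after 2 h a rise in pCO2 alone is not a listed reason to switch, while a fall is.

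The PaCO2 item in criterion (ii) describes a patient who is no longer hypercapnic. It stands where a second oxygenation threshold would be expected, so as printed the oxygenation limb rests on saturation alone.

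These are the working rules for two of the three components of the primary endpoint in an open-label non-inferiority trial. The Discussion acknowledges that individual judgement is unavoidable and says the switch and intubation criteria were made as clear as possible; the printed text falls short of that. A switch made solely because pCO2 rose after 2 h would not match the list and could be queried by monitoring.

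**Working it through.** The plan gives no figure for this point, so the check compares the printed criteria with each other and with the rest of the article, then adds two short calculations.

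**1. Direction of pCO2.**
- Study population: patients enter with pCO2 above 45 mmHg and pH below 7.35.
- Study endpoints, 1 h rule: "increase in pCO_2_ by at least 10 mmHg" is deterioration.
- Discussion, stated as the benefit: "NHF results in pCO_2_ reduction in hypercapnic patients over shorter time periods".
- Study endpoints, after 2 h: "unacceptable decrease in pH or pCO_2".

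The first three agree that high or rising pCO2 is the problem. The last reverses it, and nothing else in the article corrects it.

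**2. Reach of the after-2 h rule.** The schedule says "Within the first 24 h, data are collected at 1, 2, 4, 6, 12 and 24 h", then 36, 48 and 72 h.
- Scheduled blood gases to 72 h: 1, 2, 4, 6, 12, 24, 36, 48, 72 = 9.
- Strictly after 2 h: 7 of 9. Counting the 2 h sample: 8 of 9. The correctly worded 1 h rule covers 1 of 9.
- Share of the endpoint window: (72 − 2)/72 = 70/72 = 97%.

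These figures show how long the rule applies, not how many patients the slip affects.

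**3. What criterion (ii) describes.** Henderson-Hasselbalch, with assumed constants pK = 6.1 and CO2 solubility s = 0.030 to 0.031 mmol/L per mmHg:

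HCO3 = s × PaCO2 × 10^(pH − 6.1)

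- Boundary of the printed criterion (pH 7.15, PaCO2 45): 10^1.05 = 11.22. With s = 0.030, 0.030 × 45 × 11.22 = 15.1 mmol/L; with s = 0.031, 15.7 mmol/L. Lower PaCO2 or lower pH gives lower values.
- Entry limits (pH 7.35, pCO2 45), s = 0.030: 10^1.25 = 17.78, and 0.030 × 45 × 17.78 = 24.0 mmol/L.
- Hypercapnic picture at pH 7.15, s = 0.0307: PaCO2 60 gives 20.7 and PaCO2 100 gives 34.4 mmol/L.

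The printed pair therefore needs clearly reduced bicarbonate, i.e. a metabolic acidosis. Study population excludes one such group: "chronic dialysis with metabolic acidosis".

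**4. Would reversing the sign repair criterion (ii)?** Not usefully. Every patient has pCO2 above 45 mmHg at entry, so that threshold would hardly discriminate. The pairing with oxygen saturation, and the condition that the value persists on an inspired oxygen fraction above 0.5, point to an oxygenation measure, probably PaO2. This is an inference; the article does not confirm it.

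**The case against.** The strongest reply is that these are wording slips with little practical consequence.

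- **The endpoint does not depend on the reason.** Any switch or intubation within 72 h is failure. This stands; nobody is misclassified by the text itself.
- **The criteria are advisory.** Intubation criteria are recommended, and switching should only be considered when a criterion is met. This stands, but the switch criteria are also what monitoring checks and what footnote f ties device changes to.
- **A pCO2 rise usually brings a pH fall, which is listed.** From 60 to 70 mmHg at constant bicarbonate, pH falls by log10(70/60) = 0.067. If bicarbonate rises from 28 to 29 mmol/L, the fall is 0.067 − log10(29/28) = 0.067 − 0.015 = 0.052. This largely stands: switches resting on pCO2 alone should be uncommon, though not impossible.
- **A charitable reading exists.** The item could mean an inadequate fall in pCO2, or simply an unacceptable pCO2. The first makes one phrase mean too large a fall for pH and too small a fall for pCO2. The second needs *decrease* to apply to pH only. At best the rule is ambiguous.
- **A PaO2 limb would add little to saturation below 85%.** With an assumed standard dissociation curve (Severinghaus, Bohr coefficient 0.48), PaO2 45 mmHg corresponds to about 66% saturation at pH 7.15 and about 81% at pH 7.40. This limits the clinical effect of the second slip, but does not make the printed criterion right.
- **The slip may be only in the article.** Sites work from the full protocol, which is not shown, and enrolment began before the article appeared. This stands, and the fix depends on it.

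**Conclusion.** Both items are wrong as printed. The after-2 h switch rule reverses the direction of pCO2 over 97% of the endpoint window. The PaCO2 item in criterion (ii) describes a metabolic acidosis (bicarbonate below about 15.1 to 15.7 mmol/L under the constants assumed), not the condition under study. The reversal in the switch rule follows from the article's own text; that PaO2 was meant in criterion (ii) is only probable.

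The consequence is bounded. The endpoint definition is intact, and the article gives no rate of switches wrongly triggered, withheld or queried. No claim is made that improving patients are counted as failures, about the direction of any bias, or about the size of any effect on the risk difference. The point merits correction because the rules steer two of the three endpoint components without blinding, and switch reasons are audited against the protocol.

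**What to change.** 1. Reword the after-2 h switch criterion to *unacceptable decrease in pH or increase in pCO2*.
2. Correct intubation criterion (ii) after checking the full protocol: probably PaO2 in place of PaCO2, with the threshold confirmed by the clinical leads.
3. Confirm that the full protocol, the eCRF and the monitoring checks carry the correct wording.
4. If only the article is affected, a published correction is enough. If the full protocol carries the slip, issue a short amendment, update the eCRF and monitoring checks, and review only those switches and intubations whose sole documented reason was one of these two criteria.

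The cost is low: a correction notice or, at most, a short amendment with a targeted data query. The endpoint definition and sample size do not change.

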### Randomization, recruitment and data collection

Randomization will be performed centrally, via a secure web-based tool. The allocation to the intervention arm (randomization ratio 1:1) uses a minimization procedure with a stochastic component that takes into account trial centre, pH ≤/> 7.3 and BMI ≤/> 30 kg/m^2^. The randomization result forwarded automatically via email to the investigator and the Clinical Trial Centre Leipzig.

Adequate recruitment will be encouraged through regular Newsletters including current recruitment status, regular consultations with trial sites by the monitor/coordinating investigator and trial meetings.

The schedule of study visits and list of parameters collected can be found in Table 1. Within the first 24 h, data are collected at 1, 2, 4, 6, 12 and 24 h after which collection takes place at 36, 48 and 72 h. There is a discharge visit and one at day 7 as well as telephone visits on days 28 and 90.

**Table 1 Tab1:** Schedule for study interventions according to Recommendations for Interventional Trials (SPIRIT) indications

Examination/assessment		Treatment											Follow-up		
	Screening	Visit 0	Visit 1						Visit 2		Visit 3		Visit 4	Visit 5^**a**^	Visit 6^**a**^
Timepoint		0 h	1 h ± 30 min	2 h ± 30 min	4 h ± 30 min	6 h ± 30 min	12 h ± 60 min	24 h ± 60 min	36 h ± 90 min	48 h ± 120 min	72 h ± 180 min	discharge	day 7^**b**^ ± 1 day	day 28	day 90
Informed consent	X^c^											X^d^			
Inclusion criteria/exclusion criteria	X														
Randomization		X													
Patient characteristics (anamnesis, comorbidity)	X														
Medication	X							X^e^		X^e^	X^e^	X			
Clinical parameters (heart rate, respiratory rate, blood pressure, Borg’s scale)	X		X	X	X	X	X	X	X	X	X	X	X		
Adverse events/side-effects			X	X	X	X	X	X	X	X	X	X	X	X	X
Glasgow coma scale (GCS)	X		X	X	X	X	X	X	X	X	X	X			
Blood gas analysis (BGA): pO_2_, pCO_2_, pH, SpO_2_, FIO_2_	X		X	X	X	X	X	X	X	X	X	X	X		
Therapy according to allocated device: device parameters		X	X^6^	X	X	X	X	X	X	X	X	X	X^g^	X^f^	X^f^
Therapy: oxygen supplement		X	X	X	X	X	X	X	X	X	X	X	X^f^	X^f^	X^f^
infection parameters and biomarkers (optional)	X							X^e^			X^e^				

^a^Visits 5 and 6 are conducted by telephone

^b^Assessment of intubation; not applicable, if patient is already discharged since no intubation can be stated in this care

^c^Standard (long) version of informed consent OR concise (short) version of informed consent

^d^Standard (long) version of informed consent, if patient is still able to give informed consent

^e^All medications within the last 24 h resp. laboratory parameters any time within the last 24 h

^f^A change of device is possible, if switch criteria are fulfilled OR need for intubation criteria are met before 72 h → primary endpoint reached

^g^Ongoing treatment, if patient still hospitalized

The case report form (CRF) will be designed by the ZKS Leipzig in cooperation with the co-ordinating investigator and provided in electronic form (eCRF). In order to facilitate the documentation as per protocol in case of malfunction of the electronic system or any of its components, a paper version of the CRF (interim CRF) will be provided in the ISF (investigator site file). The data on this paper version will be transferred to the eCRF as soon as the electronic system is available again.

The eCRF must be completed shortly after each trial visit according to ISO 14155:2020 chapter 7.8.1 and to enable central monitoring of the trial data.

Access to the data base will be limited to authorised staff and patients will be identified by patient-ID only. Authorization is granted by the site’s investigator using the trial specific staff signature and delegation log. Based on the staff signature and delegation, log access to the eCRF will be granted by the responsible staff at the ZKS Leipzig. Authorised staff members on site will be able to enter and update data as well as finalise data by electronic signature during the conduct of the trial according to a trial specific concept for documentation. All entries and data changes will be tracked automatically including date, time and person who entered/changed information (audit trail). Major correction(s) or major missing data have to be explained.

Each trial centre is initiated by the clinical monitor before start of the study, which means that the implementation of the study is explained and all necessary documents are provided. During trial conduct, central and statistical monitoring procedures will be combined with on-site monitoring visits in order to achieve high protocol compliance and data quality, as well as to ensure patients’ safety and rights. All clinical data are entered by the investigators (or their designated staff) into electronic data collection forms, which are all available in the database. Access to the data base will be limited to authorised staff only after training on the database.

In case of premature termination of therapy, it is necessary to document the date (as exactly as possible), the reason of termination and the current condition of the patient. Therefore, the eCRF “End of study (ES)” has to be completed for each patient. Data entry to this eCRF page will trigger an automatic report to the responsible trial team members at the ZKS Leipzig.

After a patient has been enrolled, it is the investigator's responsibility to avoid protocol violations in order to obtain unbiased data for the trial. Those protocol violations deemed to be major are defined by the risk analysis performed before and during trial implementation and will be further detailed in separate documents belonging to the risk assessment/monitoring plan. This list can be augmented in the course of the trial. Major protocol violations will be reported to the coordination centre Leipzig, which will inform the co-ordinating investigator. All protocol violations will be documented and discussed with the responsible biometrician before closing the data base and carrying out the statistical analysis. The investigator must ensure that the recorded data are documented as per protocol. Minor variations are inevitable in clinical routine but must be documented together with a justification.

